### Secondary outcomes

Secondary outcomes are:

Evaluate appetite using the Council of Nutrition Appetite Questionnaire (CNAQ) score with EMA questions.

Sleep duration before and after a suicide attempt in intervention group during the 6-month follow-up period.

Electrodermal activity captured by waerables during EMA assessment in the intervention group.

Pooled EMA data Suicidal events and eating disorders in control and intervention group during the 6-month follow-up period.

### Digital collection, and data analysis

The “Smartcrises” platform is composed by two smartphone apps, which collect EMA data and smartphone sensors data, and a back-end server, which stores and processes them.

### EB2 app

The eB2 app collects data from inertial sensors, physical activity, phone calls and message logs, app usage, nearby Bluetooth and Wi-Fi connections, and location. Also, using Google Play Services, the app is able to access detailed activity information and nearby location data. The app was developed to run in background and the user only interacts with the app for the initial configuration. Moreover, it was designed with battery safe considerations like non-continuous recording schedule, automatic sleep/wake function, and it additionally notifies the operating system to relaunch itself when it was closed or stopped due to user’s actions or failures/reboots.

### Memind app

Memind is a smartphone application able to perform EMA. The MEmind app will assess wish to die via a self questionnaire and a computer assisted algorithm. The type and amount of food intake will be evaluated through the dynamic questions. Participants will be asked four static questions in the morning and evening while dynamic questions will be asked randomly at any one time-point during the day (at most 4 random questions from a pull of 32 questions distributed throughout the day). This application will offer questions on the quantity and quality of sleep, appetite and food intake, on the occurrence of social stress, evaluation of suicidal ideas and emotions. These questions are displayed according to a nonlinear dynamic model during participation to the study [31].

### Data collection and follow-up

#### Baseline assessment

The baseline enrolment questionnaire includes the patient’s basic demographic information including age, gender, marital status, employment status, country of birth, language spoken at home, level of education and whether they had a regular general practitioner.

Medical treatments at inclusion, as well as any changes in these treatments during follow-up, will be collected and analyzed as potential confounders. The treatments will be classified according to the classification established by the World Health Organization (ATC index). The entire lifetime diagnosis of mental disorders axis I and II according to DSM-5 will be based on existing clinical evaluation protocols at inclusion: Mini International Neuropsychiatric Interview 7.0.0. Participants will be evaluated for depressive symptomatology [32], to detect the possibility of a manic episode [33] and to evaluate their global functioning [34].

#### Outcomes measures

We will use complementary strategies to obtain the primary outcome measures and assess adverse events. Assessments will be carried out by trained clinicians (Psychologist, Psychiatrist or Psychiatrist Residents up to second year) at outpatient clinics and emergency departments.

Researchers will check the hospital attendance data especially the emergency records.

The assessment of suicidal behaviors will include at the inclusion and completion of follow-up:
The Columbia Suicide Severity Rating Scale a scale that showed good sensitivity and specificity to identify the most at risk subjects [35].If a suicide attempt has occurred, the suicide intent scale [36] and the Risk Rescue Rating Scale.

#### Suicide and sleep monitoring

Evaluation of the principal objective will be monitored via in-person interviews (see baseline assessment subsection) and EMA self-questionnaires including wish to live, wish to die, suicidal ideation, and suicide attempt during the follow-up period. The Suicidal Status Form [37] the Perceived Social Support Questionnaire (PSSQ,) and the Interpersonal Needs Questionnaire [38] have been incorporated into pop-ups to our EMA app to increase the participation rate during inactive periods [31].

The MEmind App will provide questions following a dynamic smartphone based assessment protocol exploring quality of sleep. The EB2 app will record diurnal activity that is related with sleep quality using smartphone sensors. EB2 will be validated with polysomnographic registers (see Fig. 2). EB2 is designed to collect information about the users’ physical and physiological activity level. This application has been developed for the Android mobile platform and works in combination with the arm Band. SmartPhone and the arm Band communicate via Bluetooth 4.0. This application obtains information from the user by accessing the built-in sensors in the host Android SmartPhone and the arm Band. Through the process of data logging the Sensor Logger APP records both the information from the SmartPhone and arm Band. This double recording of information by the Sensor Logger APP allows it to obtain enough information from inertial sensors to determine the user’s activity level during the recording process [39]. The heart rate signal and Galvanic skin response are also recorded to determine the emotional state of the user. In our study participants in the Smartcrisis group will be monitored with a wearable armband to assess sleep phases and physiological changes during sleep.

**Fig. 2 Fig2:**
[figure not shown]
Patient flow in intervention group

#### Food intake monitoring

Two questions in the dynamic protocol will assess appetite and food intake. Food ingestion will also be assessed and paired with activity monitoring using the arm band data.

#### Emotional state during EMA process

The wearable tracker band will record electrodermal activity at 3 time points: 5 min prior to EMA questioning; during the patient answer to EMA and 5 min after. Objective longitudinal records from patients will determine the sleep-suicide behavior casual chain based on wearables and EMA records.

### Sample size

We propose to recruit 1000 patients from two sites and expect a total of 100 suicide re-attempts during the follow-up period. We plan to recruit 500 patients per site (total of 1000) during 18 months with a follow-up period of 6 months. Based on our suicidal behavior monitoring pilot data (see above), we have calculated power in multivariate logit regression models, assuming a type I error of 0.05 and two-sided comparison. Using the effect sizes and standard deviations from our pilot data we expect our sample 1000 attempters and 100 reattempters during the follow-up) to provide 80% power to detect significant changes in death desire, suicidal ideation or suicide attempt related with sleep and appetite.

### Data analysis

We will carry out descriptive analyses of all data collected separately by site and treatment. We will calculate means, variances and empirical quartiles, and assess the distribution and skewness of the data. If groups differ significantly on covariates then these scores will additionally be included as covariates in multivariate regression models.

We will use 3 multi-level logit regression to account for multiple observations per individual, to identify individual-level (sleep, appetite, socio-demographic, clinical data, treatment data) and site-level characteristics associated with death desire, suicidal ideation or suicide attempt. We will use hazards models to relate covariate characteristics (sleep, appetite, socio-demographic, clinical data, treatment data) with time to suicide re-attempt during the follow-up period**.** Data mining (machine learning) techniques will be used to examine risk factors, patterns of illness evolution and outcomes, and patient stratification by level of risk.

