## Method and design

### Study design and setting

This study is a pragmatic, prospective, multisite controlled trial with two parallel groups. The study setting is outpatient clinics and emergency departments at four clinical centers across two countries (Jimenez Diaz Foundation, Spain, University Hospital of Nimes, France).

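### Two sites, one per country, cannot support the stated aim of identifying site-level characteristics associated with suicidal outcomes

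*Protocol article*

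**What the plan says.** The modelling plan in Data analysis begins "We will use 3 multi-level logit regression to account for multiple observations per individual". The same sentence gives the models a second purpose, "to identify individual-level (sleep, appetite, socio-demographic, clinical data, treatment data) and site-level characteristics associated with death desire, suicidal ideation or suicide attempt". The aim therefore covers characteristics of sites, in the plural, as well as characteristics of patients.

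The Sample size section gives the number of sites: "We propose to recruit 1000 patients from two sites and expect a total of 100 suicide re-attempts during the follow-up period", followed by "We plan to recruit 500 patients per site (total of 1000) during 18 months with a follow-up period of 6 months". Study design and setting gives a different count, "outpatient clinics and emergency departments at four clinical centers across two countries", but the bracket after it names only two institutions: "Jimenez Diaz Foundation, Spain, University Hospital of Nimes, France". The Method/design part of the abstract names the same two hospitals.

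The article does not say which site-level characteristics are meant, or whether site enters the models as a random or a fixed effect.

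**The concern.** What can be learned about a site-level characteristic depends on the number of sites, not the number of patients. With one hospital in each of two countries, every feature of a site (staffing, follow-up practice, language, health system) changes at the same step from Madrid to Nimes. Recruiting more patients at either hospital does not separate these features.

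The software will not signal the problem. A logit model with one site-level covariate and no other site term will run and return a p-value built on 1000 patients. If a Spain–France difference exists for any reason, the report could name a particular site feature as a suicide risk factor when the data show only that the two hospitals differ. The abstract presents the study as a comparison across nations, so such a difference is likely to be interpreted.

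**Working it through.** **Inputs.** Two sites, 500 patients each, 100 expected re-attempts, two-sided alpha 0.05 and 80% power (Sample size); four centres stated, two named (Study design and setting). Assumptions of this review, because the article gives no value: the between-site SD on the logit scale (range 0 to 0.5) and, for the four-centre reading, an even split of 250 patients per centre.

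**The plan's own figures.** 2 × 500 = 1000 agrees. The event rate is 100/1000 = 10%. The 80% power cannot be reproduced because the pilot effect sizes are not given. For one standardised covariate in a simple logit model, the implied effect is ln OR = (1.960 + 0.842)/√(1000 × 0.10 × 0.90) = 2.802/9.487 = 0.295, an odds ratio of about 1.34 per SD. This concerns patient-level sleep and appetite, and the present point does not depend on it.

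**Two sites: what is identified.**
- Intercept plus one site-level covariate: 2 parameters, rank 2, residual df at site level 2 − 2 = 0. A contrast exists, but there is no between-site error against which to test it.
- Intercept plus two site-level covariates: 3 parameters, rank 2. Not identified.
- Two site indicators plus one site-level covariate: 3 columns, rank 2. The characteristic cannot be estimated beside the site effect.
- The plain site contrast is estimable: 500 v 500 around a 10% rate gives about 81% power for 7.3% v 12.7%.

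**Two sites: reading that contrast as the effect of a characteristic.** The within-site sampling variance of the log odds ratio is v0 = 2/(500 × 0.09) = 0.0444. If sites also differ for unrelated reasons with SD τ, the true variance is v0 + 2τ². The false-positive rate for a characteristic with no effect is then 2[1 − Φ(1.96 √(v0/(v0 + 2τ²)))]:
- τ = 0: 5%
- τ = 0.1: 10%
- τ = 0.2: 24%
- τ = 0.3: 38%
- τ = 0.5: 58%

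For τ = 0.2: v0 + 2τ² = 0.1244, √(0.0444/0.1244) = 0.598, 1.96 × 0.598 = 1.17, two-sided tail 0.24.

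**Four centres.** One site-level covariate leaves 4 − 2 = 2 df (critical t 4.30), two leave 1 df (12.7), three leave none. For a covariate split two centres against two, the variance of the contrast is (τ² + 1/(250 × 0.09)) × (1/2 + 1/2). By the noncentral t with 2 df, 80% power needs an odds ratio of about 3.3 if τ = 0, 5.2 if τ = 0.2 and 21.5 if τ = 0.5.

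**Only if site were a random effect.** Chi-square limits, treating site means as known exactly, give a 95% interval for the between-site variance as a multiple of its estimate:
- two sites (1 df): 1/5.024 = 0.20 to 1/0.000982 = 1018
- four centres (3 df): 3/9.348 = 0.32 to 3/0.2158 = 13.9

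**The case against.** The strongest reply is that the article nowhere makes site a random effect. The reason it gives for the multi-level structure is repeated measurement within patients, so the stated cluster is the patient. The figure 3 in that sentence may mean three models, one per outcome, and not three levels. Site may already be a fixed term, and its coding is a detail that an article can leave to the full protocol or SAP. This stands. A reader might infer that the plan will estimate a near-arbitrary site variance that distorts its standard errors; the text does not support that, and the variance intervals above are conditional on a choice it does not state.

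A reader might also conclude that no site effect can be estimated at all. That goes too far: one Spain–France contrast is estimable, and the phrase about site-level characteristics may be loose wording for it. The limit is attribution. But the text as written asks for characteristics, in the plural, and that is what two sites cannot deliver under either coding.

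The four centres might be the outpatient clinic and the emergency department of each hospital. Setting would then not be tied to country. The article does not say so, and four units would still leave at most 2 df for a site-level covariate.

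No listed objective or outcome is site-level, and the power statement concerns sleep and appetite. That limits the importance of the point but does not remove it. Nor does a fixed site term cure it alone, since such a term still yields a patient-level p-value for Spain versus France; the interpretation has to change too. The hazards-model sentence lists no site-level covariate, so nothing there needs correction on this ground.

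**Conclusion.** The stated aim is wrong as written, within a narrow scope. With two sites, a site-level characteristic cannot be distinguished from site or country: zero residual df for one, non-identification for two or more. With four centres, one such covariate is technically estimable on 2 df but uninformative; even with no between-site variation, an odds ratio of about 3.3 would be needed for 80% power under the assumed 2 + 2 split.

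The rank and df results need no assumption beyond the number of sites. The false-positive rates and detectable odds ratios rest on the 10% event rate and the assumed site SD, and are illustrations. The conflict between two sites and four centres is a real inconsistency, and it determines how many site terms the models contain. The patient level of the models is sound, and the individual-level analyses remain feasible. The point is worth correcting but does not threaten the main analysis.

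**What to change.** 1. Reconcile the two sites in Sample size with the four centres in Study design and setting, and list the centres.
2. In Data analysis, keep patient as the random level for repeated observations, and state that site (one indicator for two sites, three for four centres) enters each logit model as a fixed adjustment term.
3. Delete the aim of identifying site-level characteristics. Report any site difference descriptively, with its estimate and confidence interval, as a Spain–France difference not attributed to any feature of the hospitals.

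The cost is a few lines of wording in the protocol, carried into the SAP. What is given up is a site-level inference that this design could not support; the sleep and appetite analyses do not change.

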## Discussion

### Data privacy

Data privacy is a serious concern in the e-health research area. Our system complies with the highest level of security regarding patients’ data. The eB2 app captures data from smartphones, which possibly was a deterrent for patients to accept the app [40]. In a preliminary study, patients were aware of the general approach of our method and were not very concerned about sharing their personal data since it was anonymized at the smartphone. Another major concern regarding personal electronic data is data security [41]. In order to preserve the patient’s privacy and reduce the risk associated to a non-legitimate access, all the sensible information stored in the eB2 server was hashed and anonymized. Phone numbers, email addresses, Bluetooth, and Wi-Fi MAC addresses were hashed using the SHA-1 algorithm and the location was transformed using a non-invertible function. We store randomly-rotated relative location coordinates, where the origin was the location that was most common during the first three days after installation (typically the patient’s home). Our apps are available via app stores, which allows us to continuously update and improve the app based on newly discovered bugs and also user feedback. However, the access to the apps contents and features is permitted only for patients accepting to participate to the study. All online self-report data are de-identified (identified by a random code, unrelated to any data protected by HIPAA). Only the PI holds the code, stored in a secure location separate from data. Personal information about potential and enrolled participants will be collected, and maintained in order to protect confidentiality before, during, and after the trial according to the terms described in the ethic committee report. These data will can be used for anciliary analysis after the study manuscript publication. Data will only be shared by the cited authors of this manuscript. Data will be anonymized before communication to other research office members .

### The burden of EMA method

Other important ethical are related to EMA method must also be considered. The matter of participant burden is one such issue. EMA methods entails a non-negligible time commitment on behalf of the participants. EMA rely on daily, or sometimes more frequent, Smartphone notifications. Notifications produce a significant increment in verified compliance when compared with an identical trial without notification. A significant eroding of compliance can be observed after 3 weeks of ecological assessment [42]. Furthermore, recording participants’ daily experiences in a continuous manner is an integral part of EMA. This approach may be significantly more invasive than asking a participant to complete a retrospective questionnaire or answering a question at a traditional interview [43]. The risk of intrusiveness into daily life is real. Receiving notifications may also inconvenience participants who are expected to complete an EMA or read information at a moment’s notice (ie, requests may occur at inopportune times).

### A paradigm shift in suicide risk prevention

This study stands out from randomized controlled trials or observational studies ailing to identify suicide risk factors.

We conducted a preliminary study showing that the eB2 system was capable of identifying mobility pattern changes, which may be used as proxies for behavioral changes and relapses in mental health [6]. We will apply the two key type of models previously tested in suicidal prediction: 1) predictive models or discriminative models and 2) explanatory or generative models. Both predictive and explanatory models use patient features to provide information on future events, such as the likelihood that a patient will attempt suicide in a given time interval. Applying these models to our database, will generation of tools to improve medical decision-making, patient outcomes, and to identify mediators and moderators within causal pathways. We will also develop latent feature models using Nonparametric Bayesian (NPB) approaches to detect the different predictive signatures. The central idea behind nonparametric Bayes (NPB) is the replacement of the classical finite-dimensional prior distributions with general stochastic processes, allowing an open-ended number of degrees of freedom in a model. Nonparametric priors have several properties that make them desirable to model data with an unknown number of characteristics of different sizes or importance.

Overall, we believe that “Smartcrises” could participate to a paradigm shift from the traditional identification of risks factors in mental illnesses to personalized prevention strategies tailored to characteristics for each patient, i.e., personalized medicine [44]. We have developed a system that is able to capture data from the smartphone’s native sensors and other wearables. AI techniques seek to answer the question: How can we build computer systems that automatically improve with experience, and what are the fundamental laws that govern all learning processes? Machine learning techniques allow processing of real-time observational information by continuously learning from data to build understanding and uncover previously unexpected associations and patterns in data. Predictive and explanatory models might use individual patient data to predict future events like the probability of a patient attempting suicide in a given time interval. Our final goal would be the identification of more general behavioral changes (online social interaction) in outpatients, which has important applications for a wide range of chronic conditions, including mental health disorders. Apart from the continuous assessment of bio-parameters themselves, smartphone-based monitoring would also allow researchers to gather information on context and environment, which may prove valuable for the interpretation of the monitored biomedical data and allow for a better preventative approaches.

## Data Availability

All datasets on which the conclusions of the paper rely should be available to readers except the source code of the smartphone apps developed for the study.

## Abbreviations

AI: Artificial intelligence
EMA: Ecological momentary assessment
ESM: Experience sampling methods
